## Abstract

**Background:**

Mental health conditions are common among non-pregnant young people with any form of diabetes, affecting diabetes self-management and increasing complications risk. Limited evidence exists on whether smartphone applications “apps” combining diabetes and mental health (MH) support can improve self-management and MH in these young people. The Apps and Peer support for a Healthy future and Living Well with Diabetes (APHLID-M) multicentre study includes two randomised controlled trials (RCTs) testing such an app, aimed at reducing distress among young adults with diabetes with and without a mental health condition (MHC).

**Methods and analysis:**

An app containing diabetes and MH resources was configured onto a pre-existing, digital health platform. Young adults aged 16–30 years with diabetes will be recruited from eight Australian outpatient clinics, screened using the Kessler Psychological Distress Scale (K10) and the Problem Areas in Diabetes (PAID) questionnaires. Based on MH status, participants will be allocated to the primary RCT (MHC group) or a nested-exploratory RCT (No-MHC group) and randomised by site to the “app” (Intervention) or “no app” (control). All participants will have access to peer support and will continue to receive standard diabetes care through their clinic. Recruitment will end once 142 participants are enrolled in the primary RCT. The primary outcome is change in psychological distress (K10), and the secondary outcome change in HbA1c, assessed at baseline and 6 months.

**Discussion:**

APHLID-M will offer valuable insights into effects of digital technology in enhancing MH (particularly distress) physical health and well-being in young people with diabetes.

## Background

1

Diabetes is a growing issue among young Australians, with >30,000 young adults aged 10–30 years registered with the National Diabetes Services Scheme, 78 % of whom have Type 1 diabetes mellitus (T1DM) [1]. Standardised mortality rates as high as 6.91 (95 % CI 5.56–8.59) and 4.59 (95 % CI 3.00–7.04) have been reported for females aged 20–29 with T1DM and type 2 diabetes mellitus (T2DM) respectively, while standardised mortality rates in similarly aged males were 2.95 (95 % CI 2.41–3.61) for T1DM and 4.00 (95 % CI 2.66–6.02) for T2DM [2]. Hospitalisation rates for severe hypoglycaemia and diabetic ketoacidosis (DKA) are also five times higher among young adults than older adults with T1DM [3]. In a metropolitan hospital in Sydney, Australia, 38 % of young adults with T1DM experienced multiple DKA episodes, and 13 % experienced severe hypoglycaemic events [4,5]. Mental health conditions are also prevalent in this cohort, affecting 58 % of those with T1DM and 55 % with T2DM [4,5] 4,5 aligning with international findings where up to 63 % of patients report symptoms of depression and 32 % experience anxiety [6]. Mortality is increased in association with acute glycaemic events, accidents and suicide [7,8]. For young women with diabetes that is not optimally managed, pregnancies can also result in increased risk of adverse pregnancy outcomes and congenital abnormalities in the offspring [9,10].

The transition from youth to adulthood brings unique challenges for young people with diabetes and is often associated with increased risk-taking behaviours, changes in living and employment situations, and heightened financial pressures [11]. This period is also associated with clinic non-attendance, insulin omission, and social isolation. Disordered eating is reported in up to 50 % of young adults with diabetes [12,13], contributing to impaired glucose management. Additionally, 80 % of Australian young adults (19–24 years) do not meet the HbA1c target of 7.0 % [14], with mean HbA1c entry of 10.2 % recorded among young adults with mental health conditions [4]. Diabetes and psychological Interventions addressing risk factors for morbidity and premature mortality have demonstrated improved outcomes in people with diabetes [15,16], however evidence of their effectiveness in young adults remains limited. Given that most young adults are proficient at using smartphones [17], digital app-based health support presents a practical solution to deliver scalable interventions, providing a conduit to maintain mental health level below the threshold for clinical intervention. Perx Health, an Australian company, has developed clinically validated health apps for chronic conditions including T2DM [[18], [19], [20]] which have also been used in cohorts of young adults [20], and has now configured an app to improve mental health and self-management of young adults with diabetes.

The Apps and Peer support for a Healthy future and Living Well with Diabetes (APHLID-M) study will test whether this “app” can feasibly improve distress, well-being and physical health (e.g. glycaemia), while reducing health care costs among young adults aged 16–30 years with diabetes.

## Research question

2

The APHLID-M study will investigate whether a mobile phone “app” - for young people with diabetes and a mental health condition, improves psychological distress, well-being and physical health (e.g., glycaemia), and reduces health care costs and burden compared with controls receiving usual care. A parallel nested exploratory study among those without a mental health condition using the same methodology will also be included to assess whether the app is of benefit to this group.

## Methods and analysis

3

### Primary and secondary outcomes

3.1

The primary outcome, psychological distress, will be measured using the Kessler Psychological Distress Scale (K10). Table 1 provides a summary of the primary and secondary outcomes. A parallel health economic evaluation will also be performed.

**Table 1 tbl1:** Primary and secondary outcomes, along with their measurement timepoints, for both the intervention and control groups in the Apps and Peer Support for a Healthy Future and Living well with Diabetes (APHLID-M) study.

Outcome Type	Outcome Variable	Measurement/collection timepoint
Primary	Psychological distress assessed using the K10 questionnaire [21]	Baseline and 6 months post baseline
Secondary	HbA1c determined by an accredited laboratory or point of care testing on blood samples collected from participants	
Secondary	Diabetes-related distress measured using the PAID questionnaire [22]	
Secondary	Weight in kg will be measured using digital scale	
Secondary∗	Total number of hospital and/or emergency department admissions	Baseline (during the six month period prior to commencing the trial) and over the six month duration of the trial
Secondary∗	Total number of hospital and/or emergency department admissions due to diabetic ketoacidosis/hyperglycaemia	
Secondary∗	Total number of hospital and/or emergency department admissions due to hypoglycaemia	

K10; Kessler Psychological Distress Scale, PAID; Problem Areas in Diabetes, ∗ assessed using electronic medical records.

### Study design

3.2

The APHLID-M study includes two multi-site randomised controlled trials (RCTs) in which young adults with diabetes identified as having a mental health condition (MHC) are randomised to receive the app containing diabetes and mental health resources (intervention) or usual care (control group). The study also includes a secondary parallel RCT where participants identified as not having a mental health condition (No-MHC) will be randomised to receive the same app (intervention) or usual care (control). The study was prospectively registered as two separate trials with the Australia New Zealand Clinical Trials Registry: Apps and Peer Support for Young 10.13039/100019769People aged 16–30 years living with Diabetes and Mental Health Conditions (ACTRN12623000734662) and Apps and Peer Support for Young People aged 16–30 years living with Diabetes but without identified Mental Health Conditions (ACTRN12623000733673).

### Study phases

3.3

#### Phase 1: app configuration and peer support groups

3.3.1

An app configuration working group, comprising endocrinologists, credentialled diabetes educators, mental health professionals (including psychiatrists and psychologists), academics, consumers, and patient group representatives was established. A list of diabetes and mental health resources, along with website links, was identified and agreed upon by the working group through a Delphi process. The app was configured onto the Perx Health platform (https://www.perxhealth.com). The Perx Health app is based on behaviour change principles including Self-Determination Theory (SDT). It incorporates elements from behavioural science and gamification to improve patient engagement and adherence to health management routines (Supplementary Material) [19]. The modified Perx app (intervention) was organised into two Health Hubs: one for participants with T1DM (Supplementary Material) and another for those with T2DM. For both Health Hubs (T1DM and T2DM) the diabetes resources were made available as hyperlinks under the headings identified in the Delphi process (Table 2). People with lived experience of diabetes (T1DM and T2DM) were invited to review the adapted app, provide feedback, and assess its quality using a validated questionnaire (User Version of the Mobile Application Rating Scale) [23]. Feedback was also obtained from local diabetes clinic psychologists.

**Table 2 tbl2:** Subject headings under which diabetes and mental health resources will be available in the configured app for the APHLID-M study.

Diabetes Resources	Mental Health Resources
Glucose Management	Mindfulness apps and Online Resources
Insulin Pumps (T1DM only)	Anxiety
Injections	Depression
Sick Days	Stress
Food	Eating Disorders
Contraception and Pre-pregnancy	General Mental Health
Living with Diabetes	

T1DM - Type 1 diabetes mellitus.

For the trial, all resources will be accessible in the Health Hubs for participants to use ad libitum over six months. Additionally, participants will receive in-app communications including SMS messages, alerts and tasks, approximately every four to five days directing them to specific resources within the Health Hub.

#### Phase 2: APHLID-M randomised controlled trials

3.3.2

##### Study sites and timetable

3.3.2.1

The APHLID-M study will be conducted across eight Australian sites with separate clinics for young adults in New South Wales (Campbelltown Hospital (lead), Liverpool Hospital, Bankstown-Lidcombe Hospital, St George Hospital, Prince of Wales Hospital, St Vincent's Hospital, Sydney Children's Hospital Westmead) and Victoria (Goulburn Valley Health).•Commence recruitment: July 2023.•Complete recruitment: April 2024.•Complete data collection: October 2024

##### Eligibility criteria and screening

3.3.2.2

Adolescents and young adults with T1DM, T2DM, or rare forms of diabetes attending diabetes outpatient clinics at any of the eight participating sites will be screened for potential enrolment in the study. Eligible patients will be: aged 16–30 years old; own a smartphone (Apple or Android); able to provide written informed consent. Patients unable to provide written or online informed consent, do not have a smartphone, or who are currently pregnant, or who do not speak English (app only available in English), will be ineligible to participate in the study. All consenting participants will receive a physical activity wearable tracker. No additional vouchers or monetary incentives will be provided.

##### Recruitment

3.3.2.3

Participants will be recruited by a Research Assistant at outpatient diabetes clinics, including transition, young adult, paediatric, and other clinics, either when attending the clinic or if on the clinic register. The Research Assistant will meet potential participants face to face or contact eligible patients via phone/email to invite them to participate.

##### Screening and allocation of participants to study groups

3.3.2.4

Participants will be screened using two validated screening questionnaires: the Kessler Psychological Distress Scale (K10) [21] and the Problem Areas in Diabetes (PAID) scale [22]. The K10 is a validated and widely used self-reported psychological screening tool consisting of 10 questions about emotional states, each with a five-point Likert response scale ranging from 1 (none of the time) to 5 (all of the time). K10 total scores range from 10 to 50 with higher scores indicating greater levels of psychological distress [21]. Participants returning a K10 score ≥20 will be classified as having an MHC. The PAID questionnaire measures diabetes-related emotional distress and is widely used in clinical and research settings [22]. The PAID questionnaire includes 20 items covering emotional challenges experienced by people with diabetes, including worries about managing the condition, fears of potential complications, and feelings of frustration or burnout. Participants returning PAID scores ≥40 will be classified as having an MHC [22]. Participants who self-report a previously diagnosed mental health history or are currently receiving care for a mental health condition from a psychologist will also be classified as having an MHC. Participants identified as having major distress (K10 ≥ 40, PAID ≥20) will be considered for referral to the site psychologist (if available) or their general practitioner for management independent of their allocated group but will not be excluded from the study. (Fig. 1). Results from the screening questionnaires will be used to allocate participants into two studies: those with a mental health condition (MHC; Primary RCT) and those without a mental health condition (No-MHC; Nested exploratory RCT).

**Fig. 1 fig1:**
[figure not shown]
Apps and Peer support for a Healthy future and Living well with Diabetes (APHLID-M) study design.

##### Randomisation and blinding

3.3.2.5

Randomisation to either “app” or “no app” within each study (MHC and No MHC) will be allocated by the database randomiser using randomisation by minimisation stratified within site. Allocation will not be concealed from participants or healthcare workers, however research staff collecting data will be blinded at baseline and follow-up. Participants assigned to the intervention arms will be onboarded to the Health Hub within the Perx app appropriate to their diabetes type. Participants will be invited to onboard via email and text message notifications (SMS) from Perx Health, which will include instructions on how to download the app and sign in on their smartphones. Research Assistants collecting data and the study statistician will be blinded to a participant's randomisation status. Allocation to the app will not be concealed from participants or healthcare workers.

##### Intervention

3.3.2.6

The intervention delivered to the MHC and No MHC studies will be identical. All participants will receive standard diabetes care through their regular clinic. This includes education sessions, a food diary, self-management practices such as blood glucose monitoring, healthy eating, regular clinic attendance with review of blood glucose monitoring and weight measurements conducted either by the educator and/or endocrinologist. Participants will receive a physical activity tracker and have access to Peer Support facilitated by people with lived experience of diabetes. Availability of Peer Support is considered part of best practice standard care [24] and will be available at the outpatient clinics of the study sites included in this trial. It is already available at some sites and will be established at sites without existing Peer Support during the trial set-up phase. Peer support can be provided digitally (e.g., ad hoc Facebook communication, Zoom meetings) or through one-on-one or group face-to-face meetings, with the topic focus, frequency and duration determined by the peers or peer support facilitators.

##### Collection of participant data

3.3.2.7

Quantitative data collected from participants in both RCTs (primary; MCH and nested exploratory RCT; No MHC) at baseline and six months post baseline is described in Table 3.

**Table 3 tbl3:** Overview of variables and data collected for the APHLID-M primary RCT (MHC) and parallel nested exploratory RCT (No-MHC). Data will be collected from young adults aged 16–30 years with Type 1 diabetes, Type 2 diabetes, or rare forms of diabetes attending specialist diabetes services across eight hospitals.

Clinical Outcomes (measured at baseline and after 6 months)	
Psychological distress	K10 [21]; Diabetes distress [22]
Quantitative data to assess metabolic management	HbA1c
	If testing/using Continuous Glucose Monitoring Sensor/Flash Glucose Monitoring System: Time in/above/below range, glucose variability; mean glucose; blood pressure; lipids; BMI; weight, height (baseline only); CVD risk-adiponectin
Hospitalisation	Number of emergency department or hospital admissions or ambulance treatment and released in the last 3 years (i) total admissions ii) diabetic ketoacidosis (DKA)/hyperglycaemia (iii) hypoglycaemia
Patient engagement	Missed outpatient clinic appointments in the past 6 months; provision of self-monitoring data;
	Medication adherence; sick day planning; hypo treatment; Contraception use; needle/set changes; app use.
Psychosocial and behavioural outcomes	The Diabetes Eating Problem Survey-Revised [DEPS-R) [25] Self-efficacy
Self-management	Summary of Diabetes Self-Care Activities (SDSCA) [26,27] Physical activity tracker time spent in low, moderate, and vigorous activity and sedentary behaviour, time spent sleeping and quality of sleep.
Patient reported outcomes	Diabetes Empowerment Scale – Short Form (DES-SF) [28]
Sample collection and storage	Samples will be taken for the measurement of total/high-molecular-weight adiponectin using a quantitative monoclonal sandwich ELISA and stored for use in future studies of diabetes and its risk factors and complications.
Cost-Utility	EQ5D-5L [29,30]; Hospital service utilisation including telephone and online occasions of service; Acute glycaemic hospitalisation/emergency department visits; Economic evaluation includes Institute for Clinical and Economic Review.
Other: includes qualitative research	Consumer and healthcare professional perspectives on the intervention and its impacts on patient, provider, and health-system implementation

HbA1c-glycated haemoglobin, BMI – body mass index, CVD-cardiovascular disease, ED-emergency department, ELISA – enzyme linked immunosorbent assay, PA-physical activity, MHC – mental health condition, No-MHC – No mental health condition.

To gain insight into participants' experiences and perceptions of using the app and its impact on diabetes management, participants randomised to the intervention from both studies will be invited to participate in focus groups or one on one interviews (online or face to face) as per the participants preference/availability. Additionally, and separately, healthcare staff from each site will be invited to participate in interviews/focus groups, to provide feedback on perceived feasibility of wider rollout of the intervention, and its long term sustainability at their clinics.

All participants (MHC and No MHC) will be invited to provide consent for linkage of their study data to the health system administrative data. Data requested from participants in the NSW sites are held in the Master Linkage Key (MLK) at the Centre for Health Record Linkage (CHeReL) and will include: Ambulance Data Collections; Emergency Department Data Collection (EDDC); NSW Admitted Patient.

Data Collection (APDC); NSW Mental Health Ambulatory Data Collection; NSW Non-admitted Patient Data Collection (NAP); and cause of death and register of death. The same data will be requested for the Victorian site (Goulburn Valley Health), from the Centre for Victorian Data Linkage. The data will be requested for the period 2019 to 2025 and to enable 3 years pre-trial and 3 years post-trial comparisons.

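### The linked-data request ends in 2025, but recruitment opens only in July 2023, so no participant can have the stated 3 years of post-trial follow-up

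*Protocol article*

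**What the plan says.** Section 3.3.2.7 (Collection of participant data) describes linkage to ambulance, emergency department, admitted, non-admitted, mental health ambulatory and death records in New South Wales, with the same data sought in Victoria. It covers both trials: "All participants (MHC and No MHC) will be invited to provide consent for linkage of their study data to the health system administrative data". On the period it says: "The data will be requested for the period 2019 to 2025 and to enable 3 years pre-trial and 3 years post-trial comparisons".

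Section 3.3.2.1 (Study sites and timetable) sets three dates: "Commence recruitment: July 2023", "Complete recruitment: April 2024" and "Complete data collection: October 2024".

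The time each participant spends in the trial is six months. Section 3.3.1 says of the app that "all resources will be accessible in the Health Hubs for participants to use ad libitum over six months", and Table 1 places the follow-up assessment six months after baseline.

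The article does not extend the linkage period anywhere else and does not define the start of the post-trial period.

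**The concern.** A request that stops in 2025 looks too short for a trial that opens in the middle of 2023. The date that decides this is the start of recruitment. The April 2024 close shows a shortfall only for late enrolees, whereas the July 2023 opening shows it for everyone.

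Two things are at stake. First, the period sent to the data custodians determines what can be analysed, and as written it cannot support the stated comparison. Second, the time available after the trial differs between participants by enrolment date and is shorter than the pre-trial period. A comparison of event counts therefore needs matched windows or an allowance for exposure time. Lower health care costs and burden are part of the research question in section 2, so use of services over a longer horizon is a matter of interest to the study.

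**Working it through.** **Inputs**

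- Linkage period: 2019 to 2025 (section 3.3.2.7). Its end is taken as 31 December 2025, the reading most favourable to the plan.
- Earliest enrolment: July 2023, taken as 1 July (section 3.3.2.1).
- Latest planned enrolment: April 2024, taken as 30 April (section 3.3.2.1).
- Time in the trial: 6 months (section 3.3.1 and Table 1).
- Stated comparison: 36 months before and 36 months after.

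**The plan's own figure.** The years 2019 to 2025 inclusive make 7 calendar years, and 3 + 1 + 3 = 7. The period would fit a trial run within 2022. It may therefore come from an earlier timetable, but that is inference; the article does not say so.

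**Before the trial.** Months available = enrolment date minus start of the period.

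| Start of period | First participant | Last participant |
|---|---|---|
| 1 January 2019 | 54 (4.5 years) | 64 (5.33 years) |
| 31 December 2019 | 42 (3.5 years) | 52 (4.33 years) |

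All exceed 36 months, so this side holds.

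**After the trial.** Months available = 31 December 2025 minus the time origin.

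| Time origin | First participant | Last participant | Share of 36 months |
|---|---|---|---|
| Enrolment | 1 July 2023: 30 | 30 April 2024: 20 | 20/36 = 56% to 30/36 = 83% |
| End of own six months | 1 January 2024: 24 | 31 October 2024: 14 | 14/36 = 39% to 24/36 = 67% |

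Counted for everyone from the close of data collection in October 2024, the figure is about 14 to 15 months (1.17 to 1.25 years). If the request stopped at the start of 2025, it would be 8 to 18 months from enrolment (0.67 to 1.51 years) and 2 to 12 months after the six months (0.17 to 1.0 years).

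The longest follow-up on any reading is 30 months.

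**What 36 months would need**

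- With the period fixed: enrolment by 31 December 2022 if counted from enrolment, or by about 30 June 2022 if counted from the end of the six months. Both precede the opening of recruitment.
- With the timetable fixed, counted from enrolment: data to July 2026 for the first participant and April 2027 for the last.
- With the timetable fixed, counted from the end of the six months: data to January 2027 for the first and October 2027 for the last.

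**The case against.** The strongest reply is that little in the trial depends on this period. The admission outcomes in Table 1 come from electronic medical records over six months before and six months during the trial, and the timetable accommodates both. The 3-year comparison is not in Table 1. The economic outcome in section 3.3.3 is quality-adjusted life years from questionnaires at baseline and follow-up. Linkage needs separate consent and is supplementary. All of this stands, and it limits the point to the linked-data comparison.

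A reader might also infer that the study will report a false fall in admissions. The article does not support that. Section 3.4 sets out no analysis of the linked data, so no comparison of raw counts over unequal windows is planned in the text. The requested data already allow equal windows if the pre-trial side is trimmed. Arms are randomised concurrently within site, so the cut-off falls on both alike and the dates show no bias between arms. What remains is conditional: unequal windows would mislead if raw counts were set side by side with no allowance for exposure time.

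It is tempting, too, to give the shortfall as one range of 14 to 30 months. That joins two time origins, and each should be reported separately.

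None of this makes the stated 3-year post-trial period attainable.

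**Conclusion.** The point holds as an inconsistency between sections 3.3.2.1 and 3.3.2.7. With data to the end of 2025, follow-up is 20 to 30 months from enrolment, or about 14 to 24 months after the six-month trial period, against 36 stated. No participant can reach 36 months; the pre-trial 3 years are available to all.

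This rests on the planned recruitment dates and on a request running to the last day of 2025. Later recruitment or an earlier end to the data would widen the gap. The conclusion does not depend on how the post-trial period is defined, because every definition falls short. The primary K10 test, the sample size and the Table 1 admission outcomes are not affected.

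**What to change.** Reconcile the two sections in one of two ways, and state the time origin of the post-trial period in either case.

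1. **Extend the request.** Ask the New South Wales and Victorian linkage centres for data to October 2027, which gives the last planned participant 3 years after the six-month trial period. The cost is an amendment with the data custodians and the ethics committee, and later delivery of the data.
2. **Restate the comparison.** Keep the 2019 to 2025 request and use equal windows that every participant can complete: about 20 months before and after randomisation, or about 14 months each side if the later window must start after the six months. The 20-month version includes the intervention period, so it should not be called post-trial. This needs no further data, but it gives up the 3-year horizon.

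Under either option, compare the arms with each other, and use log person-time as an offset if window lengths differ between participants or periods.
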